## Abstract

**Background:**

When invited for the first time at age 50, most women in Germany have to decide whether they wish to participate in the German mammography screening programme. For ethical reasons, screening decisions should be informed choices, but this is rarely the case with mammography screening. Decision aids are interventions with the potential to support informed choice by improving the following factors: knowledge, clarity of personal attitude, and implementation of an intention. Currently, no systematically evaluated decision aid exists for the German mammography screening programme. Therefore, the objective of this randomized controlled trial is to assess the effectiveness of a decision aid for first-time mammography screening programme invitees.

**Methods/Design:**

We have developed a decision aid for women invited to the mammography screening programme for the first time based on the criteria of the International Patient Decision Aids Standards Collaboration. The effectiveness of the decision aid will be evaluated in a randomized controlled trial with a 3-month follow-up. We will invite 7400 women aged 50 years from the district of Westfalen-Lippe, Germany, to participate. This sample will be drawn from registration office data. The primary outcome will be informed choice. The secondary outcomes will be the components of informed choice (knowledge, attitude, decision/implementation). Decisional conflict, decision regret, eHealth literacy, health behaviours, perceived behavioural control, subjective norms, invitation status, and demographic variables will be assessed. Data will be collected online at baseline, post-intervention, and at the 3-month follow-up. Participants will be randomized to receive either the decision aid or usual care (invitation and standard leaflet of the mammography screening programme).

**Discussion:**

This paper describes the evaluation of a decision aid for the German mammography screening programme in a randomized controlled trial. If the decision aid proves to be an effective tool to enhance the rate of informed choice, it will be made accessible to the public and the use of this decision aid for first-time invitees will be recommended. The long-term effect could be an improvement in informed choices in women invited to the mammography screening programme.

**Trial registration:**

German Clinical Trials Register DRKS00005176.

**Electronic supplementary material:**

The online version of this article (doi:10.1186/s12905-015-0210-5) contains supplementary material, which is available to authorized users.

## Background

Informed choice has become an important public health issue [1]. In the face of growing discussion about the usefulness of mammography screening [2], there is an increased need to involve women in the screening decision. For ethical reasons, their choices should be informed [3]. Despite a lack of evidence for the all-cause mortality benefit of mammography screening [4], all women in Germany between the ages of 50 and 69 are invited every 2 years to the mammography screening programme (MSP). The invitation comes with a pre-specified appointment. However, each recipient can choose whether she wishes to participate. This decision is made in the context of scientific uncertainty [5] about the extent of benefits and harms of mammography screening. Nevertheless, the accompanying information provided by the inviting organization makes it appear that choosing to attend is a more appropriate decision, thus removing uncertainty from the message. Research shows that an informed choice is not achieved in a large proportion of mammography screening decisions: Mathieu et al. arrived at the figure of 48 % informed choices [6]; van Agt et al. found 88 % [7]. Indeed, the term “uninformed compliance” [8] has been coined to describe participation in this screening. Uninformed compliance is a major public health problem in the German MSP, since many women in the target group of the MSP have unrealistic expectations regarding its potential benefits [9]. Weighing benefits against harms is a value judgment, thus no correct answer can be determined [10] making this decision preference sensitive.

To identify solutions towards increasing the proportion of women making informed choices, the dimensions of this construct must be specified. A decision is classified as informed if the decision maker has good knowledge of the situation as well as an attitude congruent with the choice, and then implements the decision [11]. Therefore, to enable an informed choice, women invited to the MSP need to be informed about the existence and probability of positive and negative outcomes and given the opportunity to clarify the meanings of those outcomes for them personally. If these two conditions are met, implementation of a decision is also more likely.

The question then is how to meet these conditions. One innovative approach to addressing the issue of uninformed compliance is the use of decision aids (DAs). It is in preference sensitive decisions that a DA is most useful though the level of detail that should be used in DAs is controversial [12].

There is ongoing discussion about how useful quantitative information in DAs is for the deciding person [13]. From an informed choice perspective, not only the existence of a benefit or harm but also its probability is important for the decision [14]. Otherwise it is not possible to weigh the different outcomes against each other.

To assess concordance in decision making, several options exist. Sepucha and Fowler [15] recommend a simple match using decision (in form of a single preference question) and implementation; this leaves out attitude (which would require several questions on the different outcomes of an option). While preference already includes a decisional element, attitude is more distal targeting the different outcomes an option has. In this study, we therefore use attitude and knowledge scores to determine decision quality.

DAs are tools that help individuals choose between “two or more medically-appropriate healthcare options” [16] (p. 2). Research has shown that DAs are a promising strategy to increase the rate of informed choices in mammography screening [6]. To date, however, few studies have examined the effect of DAs on informed choice in such screening.

For the established MSP in Germany, there are no systematically evaluated DAs. To our knowledge, the only DA that exists was evaluated with a convenience sample of n=152 in a cross-sectional study design [17]. It does not meet International Patient Decision Aids Standards (IPDAS) to a high degree. Common shortcomings of studies in other mammography screening contexts are that they analyse only the immediate effects of DAs and do not follow up on the long-term effects on knowledge and decisional conflict [18]. Additionally, they do not target the age group for which mammography screening is intended [6, 19] or assess only high-risk populations [20, 21]. Therefore, it is unclear whether a DA would be beneficial for the German MSP or what long-term effects it would have. To meet this lack of a suitable DA, we developed a DA for first-time MSP invitees.

The present study aims to assess the effect of an interactive online DA on informed choice in a randomized controlled trial using a representative sample. The primary objective is to evaluate whether the DA results in more women making an informed choice. The secondary objectives are to evaluate whether the DA (1) improves knowledge of the MSP, (2) clarifies attitudes on the MSP, (3) changes intentions to participate in the MSP, (4) is affected by background factors (e.g. education level) in its influence on the primary and secondary outcomes, (5) lowers decisional conflicts, and (6) differs in its long-term effects depending on the outcome group of the screening (true positive, false positive, negative).

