### Consent and data collection

The letter of invitation to the study, detailed study information, a consent form, and a return envelope will be sent by post 3 weeks in advance of the estimated date of receipt of the invitation to the MSP. The consent form will also provide for the possibility of specifying that the recipient does not have access to an email address. To increase the response rate, 1 week after the written invitation to participate in the study, a reminder and thank-you postcard will be mailed out.

Three weeks after the invitation is sent out, all women who gave informed consent and provided us with an email address will be emailed the link to the baseline questionnaire (T1). Women whose consent form is received 3-5 weeks after the invitation will receive the link at 5 weeks after the invitation. Women whose consent form is received later than 5 weeks after the invitation will receive the link at 7 weeks.

The link to the second assessment (T2) will be sent to participants 2 weeks after the first email. Women will be randomly assigned to the intervention or control group, and accordingly, receive a link either to the DA and second assessment or only to the second assessment. The link to the third assessment (T3) will be sent to the women 3 months after T2 when the screening appointment is assumed to have passed. A reminder and thank you will be emailed to all women who initially agreed to participate 10 days after sending the survey link at T1, T2, and T3.

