*Subjective norms* will be measured using two items developed according to the reasoned action approach of Fishbein and Ajzen [27] and rated on a five-point scale (“Most people who are important to me think that I should/should not participate in the MSP”; “Most people like me would/would not participate in the MSP”). Additionally, five items will measure normative beliefs rated on a five-point scale, ranging from “advise” to “disadvise” with the additional option of “no advice”. These items will assess the direction of advice of doctors, family, and friends.

*Decisional conflict* will be measured using the SURE (Sure of myself; Understand information; Risk-benefit ratio; Encouragement) test [28]. This four-item test with the answer options yes and no will assesses knowledge of options, clarity of importance of advantages and disadvantages, sufficient level of support, and being sure about the best choice. Since no German translation of this scale is available, the scale was translated as part of this study, and indices of reliability and validity will be published.

*Decision regret* will be measured using the Decision Regret Scale [29]. The five items will be rated on a five-point scale (“strongly agree” to “strongly disagree”). Since no German translation of this scale is available, the scale was translated as part of this study, and indices of reliability and validity will be published.

*Result of the MSP* will be assessed using two items regarding the result of the MSP and the result of further diagnostics. The answers will allow grouping into four categories: (1) negative result; (2) false-positive result; (3) true-positive result, and (4) positive result with further diagnostics pending.

*Result and acceptability of the DA* will be measured using one item assessing whether the tailored graphic in the DA was balanced, and four items will assess acceptability of the DA regarding length, amount of information (too much/too little/just right), one-sidedness (pro/balanced/against), and helpfulness in decision making (yes/neither/no).

*Invitation status* will be measured using two items assessing whether an invitation was received and whether the appointment specified in the invitation had already passed.

*Decision stage* will be measured using one item following IPDAS criteria with the answer options being “not thought about it”, “contemplating it”, “close to deciding”, and “choice already made”.

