### Sample size

Sample size was calculated using G* Power for the primary outcome (informed choice). Based on the study of Mathieu et al. [19], we determined a difference in the proportion of informed choices of 7 percentage points as the minimum clinically important difference for the power calculation. A sample size of 740 women (370 per arm based on a 1:1 allocation ratio) will enable the detection of a between-group difference of 7 percentage points given 80 % power and a 5 % (one-tailed) significance level. Allowing for an estimated response rate of 15 % and early drop-out of one-third of initial participants, we aim to invite 7400 women to take part in the study.

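### Secondary objective 6 compares decision-aid effects across screening-result groups that form after allocation, only among attenders, and with too few true positives to estimate an effect

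*Protocol article*

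**What the plan says.** In the Background, the last of six secondary objectives is to evaluate whether the DA "differs in its long-term effects depending on the outcome group of the screening (true positive, false positive, negative". Nothing there marks it as exploratory. Objective 3 in the same list asks whether the DA alters intention to take part in the programme.

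The Consent and data collection section describes allocation together with the T2 mailing: "Women will be randomly assigned to the intervention or control group, and accordingly, receive a link either to the DA and second assessment". T3 follows 3 months later. Table 1 places both uptake and result of the MSP at T3 only. Under Secondary outcome measures, uptake has three answers: the programme, opportunistic screening, or none. Result of the MSP has four categories, the last two being "3) true-positive result, and (4) positive result with further diagnostics pending".

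The Sample size section addresses the primary outcome only: "A sample size of 740 women (370 per arm based on a 1:1 allocation ratio". The Data analysis section names no method for objective 6. It plans moderation analyses, with the PROCESS macro, of the secondary and demographic variables, and MSP result is listed among the secondary measures.

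**The concern.** Asking whether an intervention works differently by subgroup is sound when the subgroup is fixed before allocation. Here it is not. A programme result requires attendance, and attendance may respond to the DA. If it does, DA-arm attenders and control-arm attenders are differently selected, and a difference between them within a result group mixes the DA's effect with that selection. The multivariate adjustment promised in the Discussion concerns selective participation in the online survey, which is a different selection.

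One of the three groups is also bound to be very small. As the plan stands, MSP result could be entered as an ordinary moderator, and the output reported as the answer to a stated objective. Readers could then draw conclusions about how the DA performs after a false alarm or a cancer diagnosis that the trial cannot support.

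**Working it through.** **The plan's own figure.** The article works from "Allowing for an estimated response rate of 15 % and early drop-out of one-third of initial participants" to the statement "we aim to invite 7400 women to take part in the study". This reproduces: 740 / 0.15 / (1 − 1/3) = 7400, that is 1110 responders and 740 after drop-out. I take 740 as the number with T3 data, which is favourable to the objective if any women are lost after T2.

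**Timing.** The study letter goes out 3 weeks before the expected MSP invitation. The T1 link follows 3, 5 or 7 weeks after the letter, and the T2 link 2 weeks after T1. The T2 link therefore arrives 2, 4 or 6 weeks after the expected MSP invitation (3 + 2 − 3, 5 + 2 − 3, 7 + 2 − 3). By design the result comes after allocation. However, T2 asks whether the appointment has already passed, so some women may have been screened before seeing the DA. The document gives no number for this.

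**Structure.** In result group g, the observed difference between arms is d(g) + b(g). Here d(g) is the DA effect, and b(g) is the difference between arms that would exist without any DA effect on the outcome, because different women attend. Randomisation makes b zero in the whole sample, but not among attenders if the DA moves attendance. The contrast in objective 6 is [d(FP) − d(NEG)] + [b(FP) − b(NEG)], and likewise for true positives. The second bracket vanishes only if attendance selection acts equally in both result groups.

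**Group sizes.** The document gives no uptake, recall or detection rate. Assumed: uptake u = 40–100%, with recall r and detection c paired as 3% and 0.3%, 5% and 0.6%, 8% and 0.8%, 10% and 1.0%. Then, for both arms together:
- true positives (TP) = 740 × u × c
- false positives (FP) = 740 × u × (r − c)
- negatives (NEG) = 740 × u × (1 − r)

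The smallest difference in standardised DA effect between two result groups that is detectable with 80% power (two-sided 5%, equal arms within groups, continuous outcome) is (1.96 + 0.8416) × √(4/nA + 4/nB), where nA and nB are the two group totals.

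| u | r | c | Attenders | TP | FP | NEG | FP vs NEG, SD | TP vs NEG, SD |
|---|---|---|---|---|---|---|---|---|
| 40% | 3% | 0.3% | 296 | 0.9 | 8.0 | 287.1 | 2.01 | 5.96 |
| 55% | 5% | 0.6% | 407 | 2.4 | 17.9 | 386.7 | 1.35 | 3.60 |
| 70% | 8% | 0.8% | 518 | 4.1 | 37.3 | 476.6 | 0.95 | 2.76 |
| 100% | 10% | 1.0% | 740 | 7.4 | 66.6 | 666.0 | 0.72 | 2.07 |

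The first and last rows are the extremes of the grid for TP, FP and both detectable differences. With a one-sided 5% test, the FP versus NEG range is 0.64 to 1.78 SD. For comparison, the main effect with 370 per arm is detectable at (1.96 + 0.8416) × √(2/370) = 0.21 SD.

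**True positives per arm.** At 55% uptake and 0.6% detection, with 203 attenders per arm, the chance of at least one true positive in each arm is [1 − 0.994^203]² = 0.50. The chance of at least two in each arm is 0.12. Ten per arm would require a detection rate of 20/740 = 2.7% at full uptake, or 20/(740 × 0.55) = 4.9% at 55%.

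Women in the pending category are not deducted here. Any such women would come out of the TP and FP columns.

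**The case against.** Four points can be made for the plan.

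- **Selection may partly cancel.** Objective 6 is a difference between groups. The DA may change who attends, but nothing suggests it changes a woman's result once she attends. If result is unrelated to the traits that drive attendance, b(g) is similar across groups and largely drops out. This stands. A reader might infer that any reported difference would have to be an artefact or noise, and the documents do not support that.
- **A shift in attendance is possible, not shown.** Objective 3 concerns intention and is an open question. Uptake is recorded at T3, so balance between arms can be inspected. This also stands, but similar uptake percentages would not show that the same kinds of women attended.
- **Part of the question can be computed.** False positive versus negative is estimable, and low power for a secondary objective is common. Correct, so it would be too strong to say that nothing can be learned. What remains is a non-randomised description with wide intervals.
- **The analysis is not spelled out.** A full protocol or SAP may deal with sparse groups. That is fair as far as method goes. The objective itself is stated here as a question about effect by group, and the general moderation plan leaves MSP result open to inferential testing.

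The pending category could be read as a contradiction of the objective's three groups. It is not: it is the proper place for results that cannot yet be classified, and it only needs to be shown.

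**Conclusion.** The point holds in a limited form. From the document alone, the grouping variable is observed after allocation, is defined only for MSP attenders, and depends on attendance that the DA may change. Comparisons of arms within result groups therefore lack the protection of randomisation. On the assumed rates, the true-positive group holds about 1 to 7 women across both arms, even allowing for full uptake. The three-group contrast as worded cannot be estimated. False positive versus negative rests on about 8 to 67 false positives, and its detectable difference (0.7 to 2.0 SD) is some three to ten times that of the main effect (0.72/0.21 = 3.4; 2.01/0.21 = 9.6).

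The group sizes depend on rates that the document does not give. The structural point does not. The matter concerns one secondary objective and leaves the primary analysis untouched. A reader might conclude that the objective should be deleted and results pooled over arms. That goes too far, because it would discard arm-specific description of women with a false positive.

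**What to change.** Reword objective 6 as exploratory and descriptive. In the analysis plan:

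- report T3 outcomes by result group and by arm, with counts and confidence intervals;
- show the pending group and MSP uptake by arm alongside;
- list true positives as counts only;
- exclude MSP result from the inferential moderation analyses;
- state that membership of a result group is selected by attendance.

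Keep the randomised comparison of long-term outcomes in all women as the basis for inference.

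The cost is a change of wording and one descriptive table. No new data are needed. The trial gives up an inferential claim on one secondary objective.

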## Methods/Design

### Design

This study is a non-blinded two-arm randomized controlled trial, since it was obvious to the participants whether they received just questionnaires or also an online decision aid. The participating women will be randomized to either (1) the DA (intervention group) or (2) usual care (control group). The random allocation will be on a 1:1 ratio basis. This study will be conducted in Wesfalen-Lippe, Germany. The usual care for women aged 50 in Germany involves an invitation from the MSP accompanied by an information leaflet (see [22]). Therefore, both study groups will receive these standard materials. The online assessments will be conducted at baseline (T1), at post-intervention (T2), and at a 3-month follow-up (T3) (Fig. 1).

**Fig. 1 Fig1:**
[figure not shown]
Trial flow diagram

### Ethical approval

Ethical approval was obtained from the Ethics Commission of the Medical Association Westfalen-Lippe and the Medical Faculty of the University of Münster. Data handling will conform to the data protection legislation of the federal state of North Rhine-Westphalia. We have also obtained approval from the data protection officer at Bielefeld University.

This research project is independent of the MSP. Invited women will be informed about the content, purpose, and procedure of the study, and we will obtain their written informed consent before proceeding. Personal data will be stored separately from research data. The first, second, and third assessments (T1, T2, and T3) can be linked to each other by means of a self-generated code consisting of the following elements: day of the month the mother was born, first letter of the first name of the mother, day of the month the father was born, first letter of the first name of the father, and first letter of own place of birth. This way the questionnaires cannot be associated with any personal data. All personal data will be deleted after completion of the study. Participation in the study will be voluntary and the participants may revoke consent at any time.

### Participants’ eligibility

Women aged 50 will be eligible for this study because they are invited to the MSP for the first time. Women who have ever been diagnosed with breast cancer will be excluded since they are not targeted by the MSP. Previous mammograms for diagnostic or screening purposes will not influence eligibility.

### Recruitment

The sample will be representative of the above-described study population in the district of Westfalen-Lippe. The data will stem from the registration offices of this district, which have consented to their data being used in this study. The sample will consist of women with birth months of March to May 1964. We will make the following random selection from our data pool: 2000 women with the birth month of March, 2000 women with the birth month of April, and 3400 women with the birth month of May. The sampling will take place (drawing without replacement) after the sampling of another study—Informed Choice of German and Turkish Women for Participation in the MSP (InEMa) [23]. All women with a positive name algorithm for a Turkish migration background have been assigned to the InEMa study (see [24] for information on the name algorithm). Therefore, the sample for the present study will be drawn from a data pool without positive name algorithms. Accordingly, no women with a Turkish migration background will be present in our sample, and this factor will be considered in the analysis and interpretation of the results.

